### 3. Background

People experiencing homelessness are some of the most marginalised and disadvantaged individuals in UK society. Due to unstable housing, they experience significant social and economic challenges (e.g., poverty, social exclusion) which places them at greater risk of a range of acute and chronic health problems, as well as problem substance use and severe mental health challenges [1,2]. The European Typology of Homelessness and Housing Exclusion (ETHOS) definition of homelessness takes into consideration a range of living situations, including rooflessness, houselessness, and insecure or inadequate housing [3]. In 2022/23, in Scotland there were approximately 53,111 people experiencing homelessness [4], while in England there were approximately 271,000 [5]. Tri-morbidity, the co-occurring experiences of poor mental and physical health and problem substance use [6], is common, with use of alcohol and drugs sometimes contributing to someone becoming homeless, and often increasingly as a way of coping with homelessness [7].

For people experiencing homelessness, accessing healthcare and treatment can be particularly challenging due to stigma, negative attitudes from staff, and inflexible services [8,9]. While many people who experience homelessness are registered with primary healthcare, they are not always able to access it when needed, and frequently call on emergency healthcare services to meet their needs [10]. Recent evidence suggests that those who miss primary healthcare appointments are more likely to have mental health problems, including problem drug and/or alcohol use, and are eight times more likely to die prematurely than those who attend appointments [11]. Harm reduction, peer-delivered, and trauma/psychologically informed approaches have shown considerable promise for positively delivering care to these individuals. Therefore, the SHARPS intervention draws together these three conceptual frameworks together to create a co-produced, peer-led, relational, harm reduction, and psychologically informed environments intervention.

Harm reduction is an evidence-based approach to meeting people's needs and reducing the harms associated with substance use without the requirement of cessation of use. It embodies a non-judgemental response to substance use and aims to meet people 'where they are at' [8]. For those who are experiencing homelessness and using substances, harm reduction approaches include: overdose awareness training and naloxone; safe supplies of injecting equipment; drug consumption rooms; and non-abstinence-based housing [8]. Services embodying a harm reduction ethos provide opportunities for developing trusting and reliable relationships between staff and clients and can enable clients to feel accepted develop self-worth and increase access to care [12]. The involvement of peers, those with lived experience of phenomena such as homelessness and/or problem substance use (in this trial this does not include family related experiences), is an important aspect of harm reduction for those who are marginalised, such as those experiencing homelessness and problem substance use [8]. Meaningful involvement of people with lived experience in the design, implementation and evaluation of services is a key principle of harm reduction [13]. Due to space restrictions, we use the terms peer support, peer-led or -delivered services interchangeably, despite key differences.

Several systematic reviews have examined the key outcomes of peer support interventions that are relevant to our trial to assess clinical and cost effectiveness. Evidence shows that peer support can reduce substance use and related harm [9,14] and improve quality of life [9,15,16], mental health [16], social functioning [17], housing/homelessness status [9,16], vocational outcomes [14,16], treatment engagement/acceptability [17,18], access to healthcare [19], engagement with overdose prevention activities [20], retention during COVID-19 isolation [21], and benefit peers themselves [9,22]. One peer support intervention for people with mental health problems showed higher satisfaction with mental healthcare and improved self-reported recovery [23]. A systematic review [24] identified 36 different roles of peers specifically in drugs harm reduction, where involvement of

peers is beneficial in facilitating service engagement and reducing drug-related deaths. In terms of NHS-related policy/practice developments, recent NICE guidelines [25] on integrated services for people experiencing homelessness have highlighted the need to offer peer support, providing role modelling, supporting attendance at appointments, navigating services, forming trusting relationships, and providing advocacy to facilitate continued engagement with services. Challenges for peer workers include power imbalances, high stress, stigma, and exposure to traumatic events [20]. Previous research provides insight into how to best support peer workers, specifically at the intersection of homelessness and problem substance use [26]. Findings indicate that it is critical to provide appropriate training, personal, professional career development opportunities, and nurture relationships between peer workers, and between staff and peer workers [26]. There are also specific challenges that peer workers face when supporting individuals with complex needs including experiencing emotional and stressful situations and setting boundaries [26].

Homelessness settings in the UK are becoming increasingly psychologically/trauma informed, with many services now embedding a psychologically informed environments (PIEs) approach [8,27]. Taking a PIEs approach means understanding how people think, feel, and behave, based on their experiences and environmental factors, including trauma, and using this to inform the design and delivery of appropriate services [8,27]. PIEs involve five key areas: developing greater psychological awareness of people's needs; valuing training and support for all staff, volunteers, and clients; promoting a culture of learning and enquiry, including in service evaluation and improvement; enabling 'spaces of opportunity' which seek to create effective service environments; and a focus on the rules, roles, and responsiveness of the service which focuses on managing and improving relationships [8]. While generally from small or non-randomised studies, there is some evidence that accessing services that are PIEs-informed can lead to improvements in: client mental health and well-being, housing, and behavioural outcomes; engagement with health, substance use, and other care services; as well as reduced involvement with criminal justice and emergency services [8,28–31]. Prior to the trial reported here, there has been a lack of application of PIEs to the field of substance use, a notable research gap. In addition, while peer support appears to be important within a PIEs framework, there is limited evidence regarding the effectiveness of combining the two [8,29,32].

### **3.1 Research gap and the SHARPS feasibility study**

Despite increasing recognition of the value of peer support, and a growing evidence base [14], there are no trials reported in homelessness and substance use. This is in part due to the complexity of conducting trials with this population, given that they are commonly excluded from environments where trials might be conducted [33]. Because trial evidence supports the use of peers within mental health interventions [23,34], there is now a need for an outcomes trial focused on people who experience homelessness and problem substance use to assess effectiveness and cost-effectiveness of peer support interventions.

Our prior feasibility study examined whether a peer-delivered, relational intervention provided by salaried Peer Navigators who received bespoke training was acceptable for people experiencing both challenges, and feasible to deliver in third sector homelessness settings in Scotland and England. The co-produced intervention was created with a team of experts, including those with lived experience, combining evidence on peer support, tri-morbidity, harm reduction, and PIEs [27]. Our study HTA monograph has been published with the findings from the study, alongside three papers [8,35–37]. Our independent Study Steering Committee judged that the SHARPS feasibility study was successful, met its aims, and answered the research questions, with no documented adverse events. They recommended to the NIHR to progress to commission a full next stage trial taking forward the learning to benefit this underserved population with multiple and complex needs.

In the feasibility study, four Peer Navigators were employed to support individuals (n = 68 intervention participants) for up to 12 months based in outreach services and hostels run by three third sector organisations in Scotland and England. Qualitative interviews were conducted with intervention participants, Peer Navigators, and staff in services. Observations were also conducted in both intervention and matched standard care settings. Quantitative outcomes relating to participants' substance use, physical and mental health, and quality of the Peer Navigator relationship, were measured via a 'holistic health check', with six questionnaires completed at two time-points: one at baseline and one at the end of the intervention. The intervention and research processes were found to be acceptable to, and feasible and accessible for, participants, Peer Navigators, and service staff. Participants reported improvements in service engagement and feeling more equipped to access services independently. The lived experience of the Peer Navigators was highlighted as particularly helpful, enabling trusting, authentic, and meaningful relationships to be developed. Some challenges were experienced in relation to the 'fit' of the intervention within some settings, including the crossover between Peer Navigator and support worker roles, lack of role clarity, and tensions between staff and Peer Navigators.

While the SHARPS feasibility study was not designed or powered to produce definitive data on effectiveness, participants did report experiencing a range of positive outcomes, including reductions in drug use and risky injecting practices, and there was an increase in the number of participants receiving opioid substitution therapy. Crack cocaine use was reported as falling from 52% to 37% over a 6–8-month period, as was gabapentinoid use (34% to 23%). While two participants had experienced an overdose in the last month at baseline, no participants reported an overdose in the last month at follow-up. The mean scores for mental health outcomes (Patient Health Questionnaire, PHQ-9, Generalised Anxiety Disorder, GAD-7) improved overall, and the combined score of these (PHQ-ADS) demonstrated a reduction in the severity of self-reported depression and anxiety for many. Physical health also improved at follow-up [8]. Collection of baseline and follow-up measures was successful, with data for n=45 available at baseline and n=30 for baseline and follow up. Retention was also good: 78% engaged throughout the intervention period (and with the research process). Finally, views gathered from qualitative interviews with a sample of participants on randomisation for a future randomised controlled trial (RCT) and data linkage (across health/social care service use) were, overall, positive, with participants seeing the value of conducting a RCT provided that clear information was available on what involvement would entail. When asked whether they would agree to having their data linked, the majority agreed.

Through our feasibility work we have developed a good understanding of the potential benefits of delivering the SHARPS intervention to those experiencing homelessness and problem substance use. A full RCT is now required to fully explore the impacts on outcomes such as mental health and quality of life, and the cost implications of rolling out this intervention across services.

## **4. Aims and objectives**

### **4.1 Aim**

To evaluate the effectiveness and cost-effectiveness (compared with standard homelessness care) of a 12-month Peer Navigator-led, co-produced, relational, harm reduction and PIEs intervention for adults who are experiencing homelessness and problem substance use, for improving mental health, quality of life, and related outcomes, within social care settings.

### **4.2 Research question**

Is a peer-led harm reduction relational 12-month intervention for problem substance use among people experiencing homelessness, delivered in social care settings, effective in improving mental health, quality of life, and related outcomes, and cost-effective, compared to standard care?

### **4.3 Primary objective**

1. Conduct a 2-arm pragmatic cluster RCT (cRCT) across social care homelessness settings in 20 cities/towns in England and Scotland to determine whether the 12-month SHARPS intervention improves mental health and quality of life (co-primary outcomes), compared to standard homelessness care, in adults who are experiencing homelessness and problem substance use.

### **4.4 Secondary objectives**

1. Compare secondary outcomes, including substance use/harms, risk-taking behaviour, social functioning/support, physical health, homelessness, therapeutic alliance, and relational empathy;
2. Undertake a cost-utility and cost-consequence analysis of the SHARPS intervention.

### **4.5 Process evaluation objectives**

1. Conduct a process evaluation guided by MRC guidance and Normalisation Process Theory (NPT) to examine transferability, context, and intervention 'fit';
2. Assess intervention adherence/fidelity via mixed methods;
3. Examine Peer Navigator outcomes/experiences via mixed methods.

## **5. Design**

The study is a 2-arm pragmatic cRCT delivered across 20 clusters (cities/towns) in England (Birmingham, Blackburn, Blackpool, Bradford, Bristol, Coventry, Grimsby, Liverpool, London, Reading, Sheffield, St Helens, Sunderland, Warrington) and Scotland (Aberdeen, Dundee, Edinburgh, Glasgow, Inverness, Perth), with embedded economic and process evaluations involving mixed methods including qualitative interviews (participants, service staff, Peer Navigators), and participant consent for future data linkage to longer term health outcomes. Twenty-five participants from each intervention cluster and between 25-35 participants from each control cluster will be recruited to the study (to address the potential for greater attrition in these sites).

Outcomes will be collected at 6-, 12- and 15-months post baseline data collection. Outcomes from the Peer Navigators will be collected at 12- and 15-months post baseline data collection. A mixed methods approach will be used throughout the trial.

## **6. Eligibility**

### **6.1 Inclusion criteria**

Cluster inclusion criteria: The Salvation Army homelessness services in a town or city collectively willing to be randomised to control or intervention. All clusters were selected by The Salvation Army and the study team prior to the trial start date.

Participant Inclusion criteria: >18 years and experiencing/at risk of homelessness (ETHOS definition [3]); self-reported problem substance use and meet the pre-determined cut-off based on the ASSIST-Lite screening tool; able to provide informed consent. Prospective participants will complete the ASSIST-Lite screening tool for health and social care services, if they meet the cut-off (scored as increasing risk for any substance including alcohol) then they will be eligible to take part in the study. The level and nature of problem substance use will vary between individuals. It is anticipated that, as with our feasibility work, most participants will be experiencing problem substance use that is severe and has an ongoing and substantial impact on their daily lives. Potential participants who are under the influence of alcohol/drugs affecting their immediate ability to consent (but who do not

have long-term/permanent cognitive impairment) will be re-approached to participate and consent one or two days later. Those who are under the influence will be mentioned to service management from the point of view of safeguarding to ensure that they are provided with the appropriate support. If a participant is under the influence at the time of the data collection, or otherwise unable to undertake these measures, this will be rearranged a minimum of three times before they will be withdrawn from the study.

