Exit qualitative interviews will be conducted with a sub-sample of n=40 (n=20 at 12 months and n=20 at 15 months) intervention participants. Those participating in an exit interview will receive a separate PIS, consent form and debrief sheet. This is only relevant for the intervention participants.

Quantitative data collection will occur at baseline, and 6, 12, and 15 months after recruitment for both intervention and control groups.

Participants will be able to leave the trial at any time but will not have their trial status changed by researchers (or by the Peer Navigators) based on either continued substance use, abstinence, or lack of engagement with their Peer Navigator (loss of contact is different from lack of engagement see below). Withdrawal processes will be clearly explained in the PIS and participants will be provided with information regarding how to contact the study team, if required. Participants may become ineligible, however, and need to be withdrawn from the trial. This may relate to changes in behaviour (for example displaying violence/aggression towards the Peer Navigator that was not apparent at recruiting into the trial), loss of contact over a period of time, or in relation to capacity to consent to trial conditions. In these cases, participants will be informed by the Peer Navigator, Service Manager/Programme or Project Manager, or member of the research team, that they are no longer able to continue in the trial and a Change of Status form will be completed. Participants in the intervention arm may also move away from the city/town during the course of the study. In such cases they may still be able to continue in the trial and work with the Peer Navigator. The most appropriate option will be discussed between the Peer Navigator and participant and the Peer Navigator, Service/Programme/Project Manager and Study Leads.

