## **8.2 Control group**

The Salvation Army services within clusters assigned to the control arm will not have Peer Navigators. Instead, participants will receive the local care (standard care) pathway within The Salvation Army services. While standard care within these settings may vary between areas it usually involves having support workers help those attending services with a range of issues for example with housing applications, with contacting relatives, or wider support services. The qualitative process evaluation will systematically describe standard care at baseline, including any variations across all control sites, and any changes over the course of the trial.

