## **10. Withdrawal of consent**

Participants will be able to withdraw from the intervention at any time. Where participants wish to withdraw, clarification will be sought as to whether they wish to withdraw from receiving the intervention, short-term data collection (6 months), medium-term data collection (12 and 15 months) or a combination. All changes in status, except for complete withdrawal of consent, means the participant is still followed up for all trial outcomes wherever possible. Changes in status will be recorded on an electronic form and returned to the trial office in Stirling by email. All data collected up to the point of complete withdrawal are retained and used in the analysis. In addition, the Study Leads may discontinue a participant from the study at any time if they consider it necessary for any reason, for example if they later become ineligible due to changes in behaviour, loss of contact, or capacity. When participants initiate withdrawal from the study, they will be asked to provide a reason which will be recorded on the change of status form.

Following informed consent, if a participant loses capacity, the consent given when capable remains legally valid. In such circumstances, a decision needs to be made, in conjunction with the participant and any family or carers/Service Managers, in relation to ongoing participation in the study.

Participants will not be withdrawn by research staff based on either continued substance use or abstinence. Disengagement or limited interactions with the assigned Peer Navigator will also not be cause for withdrawal from the trial (as long as some contact is maintained to allow data collection for the trial). Efforts will be made to collect data unless participants express a wish to withdraw completely from the trial.

Clusters will not have the option to withdraw as they are designated sites as selected by The Salvation Army to take part in the trial. The only exception to this would be if all The Salvation Army services within the cluster are decommissioned, in which case we would put in place our advance contingency measures depending on how far into the trial period this takes place. The study team will be actively tracking the risk of potential decommissioning before and through the course of the study.

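### Sections 6.1 and 7.3, and the discontinuation clause in Section 10, end study participation in cases where Section 10 also says outcome follow-up continues; followed literally they discard recoverable outcomes for reasons plausibly related to those outcomes

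*Protocol*

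**What the plan says.** Three places in the Protocol end participation without the participant asking for it.

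- **Section 6.1 (Inclusion criteria).** If someone is under the influence at data collection, or for another reason cannot do the measures, "this will be rearranged a minimum of three times before they will be withdrawn from the study". The sentence names no time point and no arm.
- **Section 7.3 (Informed consent).** "Participants may become ineligible, however, and need to be withdrawn from the trial". The grounds are behaviour, lost contact over time, and capacity. The behavioural example is "displaying violence/aggression towards the Peer Navigator that was not apparent at recruiting into the trial". Such people are told that "they are no longer able to continue in the trial and a Change of Status form will be completed".
- **Section 10 (Withdrawal of consent).** The Study Leads may discontinue a participant from the study for any reason they consider necessary, with the same three grounds as examples.

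Section 10 also contains the opposite rule: "All changes in status, except for complete withdrawal of consent, means the participant is still followed up for all trial outcomes wherever possible". It repeats the idea later, saying that data will be sought unless the participant wants to leave the trial completely. It adds: "Participants will not be withdrawn by research staff based on either continued substance use or abstinence".

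Analysis is by intention to treat (Section 14.3). The primary model has baseline score as a covariate and relies on outcomes being missing at random. Section 14.6 says that assumption is unlikely to hold here and plans pattern-mixture sensitivity analyses.

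**The concern.** Field staff cannot follow both sets of instructions. A Change of Status form completed under Section 7.3 tells the participant that they are out; the same form under Section 10 means that they are still followed up.

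If the withdrawal wording prevails, a participant who could not be assessed at 6 months is not approached at 12 months, the primary time point. Because baseline enters the model as a covariate, someone with no later outcome supplies no outcome record and leaves the primary analysis, despite the intention-to-treat principle. Had only the 6-month visit been recorded as missed, a 12-month value might still have been obtained.

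Repeated intoxication at visits, disturbed behaviour and loss of contact are plausibly linked to PHQ-ADS and ICECAP-A. The rule would therefore add informative missingness that can be avoided to a trial already expecting up to 40% and 50% attrition. The planned pattern-mixture analyses can explore the consequence, but they cannot replace data that the protocol stopped collecting.

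**Working it through.** **1. The passages side by side**

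| Situation | Sections 6.1, 7.3 and discontinuation clause of 10 | Follow-up rule of Section 10 |
|---|---|---|
| Unable to complete measures after at least three rearrangements | Withdrawn from the study | Still followed up |
| Later ineligible (behaviour, lost contact, capacity) | Cannot continue in the trial; Change of Status form | Still followed up, as a change of status |
| Study Leads consider it necessary | Discontinued from the study | Still followed up unless consent is completely withdrawn |

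For withdrawal that the participant starts, Section 10 separates stopping the intervention from stopping data collection. For removal by the team no section makes that separation, and this is where the conflict arises.

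**2. The plan's own power figure**

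Inputs from Section 14.1: 250 × 0.6 = 150 and 300 × 0.5 = 150 analysed; mean cluster size 15; ICC 0.01; target 0.4 SD. Two-sided 5% is assumed, because alpha is not stated.

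- Design effect = 1 + (15 − 1) × 0.01 = 1.14.
- Effective n per arm = 150 / 1.14 = 131.6.
- Standard error = √(2 / 131.6) = 0.123 SD.
- Power = Φ(0.4 / 0.1233 − 1.96) = 90.05%.

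The stated 90% reproduces and is not in dispute.

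**3. Outcomes lost (rates assumed)**

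If 2 to 10% of the 550 recruits (11 to 55 people) meet these rules and would otherwise have given 12-month data at the average rate of 300/550, the loss is 300 × 0.02 = 6 to 300 × 0.10 = 30 outcomes.

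A harsher case assumes that every affected recruit would otherwise have been observed, and that all are lost on top of the planned attrition in both arms. With n per arm, each arm's variance is [1 + (n/10 − 1) × 0.01] / n.

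| Extra loss (share of recruits) | Analysed, intervention / control | Power |
|---|---|---|
| 2% | 145 / 144 | 89.1% |
| 5% | 137.5 / 135 | 87.5% |
| 10% | 125 / 120 | 84.3% |

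**4. Bias (rates assumed)**

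Let q be the share of otherwise observed participants removed in each arm, and k how much worse, in SD, their outcomes are than the model predicts. With the same k in both arms, bias = (q in intervention − q in control) × k.

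- Low: 0.02 × 0.5 = 0.01 SD.
- High: 0.05 × 1.0 = 0.05 SD.

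That is 0.01/0.4 = 2.5% to 0.05/0.4 = 12.5% of the target effect, and 0.01/0.123 = 0.08 to 0.05/0.123 = 0.41 of a standard error. The Trial summary's 5 PHQ-ADS points at 0.4 SD imply an SD of 5/0.4 = 12.5, so the range is 0.125 to 0.625 points. The sign follows the sign of the arm gap, which the documents do not give. With equal shares and equal k the bias is zero.

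**The case against.** **Baseline only.** The Section 6.1 sentence sits under inclusion criteria, straight after the text on re-approaching intoxicated people for consent, so it could be meant for baseline. It does not say so. It refers to data collection and leaving the study in general terms, and Section 7.3 has a separate reconsent route for people who consented but did not complete baseline. The scope is unclear, and that is itself a reason to amend it.

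**A coherent reading exists.** Section 7.3 uses a Change of Status form, and Section 10 keeps people with a changed status in follow-up. The Protocol also seeks data outside the visit window (Section 11.1). This shows the likely intent, but it does not remove the instruction that the person cannot continue in the trial.

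**One arm only.** A reader might infer that difficult participants are removed from the intervention arm alone, which would favour the intervention. It is true that "The Salvation Army services within clusters assigned to the control arm will not have Peer Navigators". But aggression towards a Peer Navigator is only an example under a clause that says participants may become ineligible. The general grounds apply in both arms, and so does the intoxication rule.

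**A second contradiction.** A reader might also set Section 6.1 against the sentence that nobody is withdrawn for continued substance use. Being unable to complete measures at a visit is not the same ground, so that tension is one of effect only.

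**Size.** The rates are assumed. People repeatedly unable to complete measures may be less likely than average to give later data, and the planned attrition may already include them. This objection stands.

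**Conclusion.** The concern holds as a direct conflict between Sections 6.1, 7.3 and the discontinuation clause of Section 10 on one side and Section 10's follow-up rule on the other. Followed literally, the former discard outcomes that could be recovered and add avoidable informative missingness to a primary model that is valid under missing at random.

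The size cannot be derived from the documents. Under the assumed rates the bias is 0.01 to 0.05 SD, less than half a standard error, and the net direction is unknown. The effect on power is modest unless the rate is high. The documents do not support a claim of one-sided bias towards the intervention. The correction is still worth making early, because a 12-month outcome that was not sought cannot be collected afterwards.

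**What to change.** Reconcile the three sections in line with Section 10's own follow-up rule.

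- **Section 6.1:** after the rearranged attempts, record that time point as missed, with the reason, and approach the participant again at each later time point. If the sentence is meant for baseline only, say so.
- **Sections 7.3 and 10:** state that discontinuation by the study team or services is a change of status that does not by itself end outcome follow-up. Whether intervention contact continues is a separate matter for those responsible, and no rule for it is proposed here.
- **End of follow-up:** outcome collection ends on the participant's complete withdrawal of consent, or where Section 10's loss-of-capacity process or a safety concern precludes it. A rule that only withdrawal of consent can end data collection would go too far, because it would override that process.
- **Change of Status form:** add a field for the reason, for use in the pattern-mixture analyses.

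The cost is wording in three sections, one form field and a few more contact attempts at later visits.
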